## Abstract

**Background:**

In wheelchair users with a chronic spinal cord injury (WU_SCI_), prolonged nonactive sitting time and reduced physical activity—typically linked to this mode of mobility—contribute to the development or exacerbation of cardiorespiratory, musculoskeletal, and endocrine-metabolic health complications that are often linked to increased risks of chronic pain or psychological morbidity. Limited evidence suggests that engaging in a walking program with a wearable robotic exoskeleton may be a promising physical activity intervention to counter these detrimental health effects.

**Objective:**

This study’s overall goals are as follows: (1) to determine the effects of a 16-week wearable robotic exoskeleton–assisted walking program on organic systems, functional capacities, and multifaceted psychosocial factors and (2) to determine self-reported satisfaction and perspectives with regard to the intervention and the device.

**Methods:**

A total of 20 WU_SCI_, who have had their injuries for more than 18 months, will complete an overground wearable robotic exoskeleton–assisted walking program (34 sessions; 60 min/session) supervised by a physiotherapist over a 16-week period (one to three sessions/week). Data will be collected 1 month prior to the program, at the beginning, and at the end as well as 2 months after completing the program. Assessments will characterize sociodemographic characteristics; anthropometric parameters; sensorimotor impairments; pain; lower extremity range of motion and spasticity; wheelchair abilities; cardiorespiratory fitness; upper extremity strength; bone architecture and mineral density at the femur, tibia, and radius; total and regional body composition; health-related quality of life; and psychological health. Interviews and an online questionnaire will be conducted to measure users’ satisfaction levels and perspectives at the end of the program. Differences across measurement times will be verified using appropriate parametric or nonparametric analyses of variance for repeated measures.

**Results:**

This study is currently underway with active recruitment in Montréal, Québec, Canada. Results are expected in the spring of 2021.

**Conclusions:**

The results from this study will be essential to guide the development, implementation, and evaluation of future evidence-based wearable robotic exoskeleton–assisted walking programs offered in the community, and to initiate a reflection regarding the use of wearable robotic exoskeletons during initial rehabilitation following a spinal cord injury.

**Trial Registration:**

ClinicalTrials.gov NCT03989752; https://clinicaltrials.gov/ct2/show/NCT03989752

**International Registered Report Identifier (IRRID):**

DERR1-10.2196/19251

## Introduction

### Deleterious Effects of Nonactive Sitting Time and Reduced Physical Activity

Approximately 100,000 Canadians are currently living with a *spinal cord injury* (SCI) and nearly 4000 new cases are reported annually in Canada [1]. Individuals affected by an SCI usually experience sensory, motor, and autonomic impairments that challenge their walking and walking-related abilities. Despite intensive initial rehabilitation, regaining effective walking ability is challenging for most [2,3]. Indeed, many individuals will not regain their ability to walk due to trunk and lower extremity paralysis or severe paresis. For others, the cardiorespiratory, muscular, or balance requirements needed to walk are too great to achieve a sufficient distance (~183-677 m) or velocity (~0.44-1.32 m/s) for ambulation within their home or in the community [4]. Hence, they will generally use a powered or manually propelled wheelchair as their main mode of mobility. The prolonged, nonactive sitting time [5] and the reduction or cessation of physical activity [6,7] typically linked to this mode of mobility contribute to the development or exacerbation over time of complex and chronic secondary health problems. These health problems often effect the cardiorespiratory [8-12], musculoskeletal [13-17], and endocrine-metabolic [18-23] systems. Moreover, they are often coupled with raised risks of nociceptive or neuropathic pain [24,25] or psychological morbidity [26] (eg, increased depressive symptoms). In turn, these negatively affect functional skills and capacity as well as psychosocial factors in long-term *wheelchair users with a chronic SCI* (WU_SCI_) [27], while also increasing the risk of premature mortality and the burden on caregivers. It is no surprise that these impacts come with substantial financial costs, estimated to be between CAD $1.5 million and $3 million (~US $1.1-$2.3 million) per person with an SCI in the Canadian health care system [28].

### Inventory of Rehabilitation and Physical Activity Interventions

Given the increased life expectancy owing to improvements in medical treatment, along with the growing population of individuals with SCI, there have been recent calls to direct additional attention to the cascade of cardiorespiratory, musculoskeletal, and endocrine-metabolic health problems faced by this population and to interventions targeting modifiable factors linked to these problems [29-31]. To date, most rehabilitation and physical activity interventional studies aiming to mitigate these health problems can be grouped within three main categories: (1) static standing activities using frames with or without full-body vibrations [32], (2) dynamic standing activities combining braces, body-weight support, functional electrical stimulation, or robotic exoskeleton systems for treadmill ambulation with various degrees of lower extremity weight bearing [33-36], and (3) lower extremity or trunk neuromuscular electrical stimulation for cycling or rowing in a sitting position [37,38]. Scoping and systematic reviews confirm that most of these interventions were tested among relatively small and heterogeneous samples of individuals with SCI over relatively short periods of time (ie, ≤12 weeks) [30]. They also highlight that superiority, equivalence, and noninferiority trial designs have rarely been used and no clear consensus has yet emerged on the best possible interventions for a given individual at a specific time within the continuum of care [30]. Nonetheless, based on the currently available evidence, it is relatively well established among WU_SCI_ that the following is true:

Gravity-derived high-standing loads, as well as impacts resulting even from low walking speeds [39], are the prominent sources of adaptive stimuli for bone health and surpass the effects linked to static standing or resistance training alone (eg, functional electrical stimulation) [40].Two to three sessions per week of regular structured exercise at moderate-to-vigorous intensity for at least 20 minutes, plus upper body strength exercise (ie, three sets of 10 repetitions at 50%-80% of the one-repetition maximum for large muscle groups), improve cardiorespiratory and endocrine-metabolic health [41-43]. Increasing this exercise intensity is expected to potentiate these beneficial effects [44].

### Wearable Robotic Exoskeletons as a Promising Intervention

Commercially available wearable robotic exoskeletons, an assistive technology allowing WU_SCI_ to stand and walk overground (see Figure 1), now offer opportunities for clinicians and scientists to develop novel activity-based physical activity programs articulated around overground walking and walking-related abilities [45,46]. Though only small-scale studies are currently available, including a feasibility study from our lab, with most focusing on walking performance [45-54], emerging evidence suggests that performing sit-stand transfers, standing, and walking with a wearable robotic exoskeleton promote lower extremity mechanical loading and mobility. The gravity exposure and muscle elongation-relaxation cycles at the lower extremities signal the mechanosensitive osteocytes and regulate the bone remodeling process via bone formation and reabsorption (ie, mechanotransduction process) [55]. Additionally, the performance of these functional abilities with a wearable robotic exoskeleton solicits the large trunk, thoracohumeral, and upper extremity muscles [56] (ie, *strengthening exercise*) via three mechanisms: (1) maintenance of standing balance, which is even more difficult as the center of mass is moved upward and backward given the configurations of the wearable robotic exoskeleton, (2) control of anterolateral body-weight shifts required to safely initiate the steps, and (3) unloading lower extremities to smooth heel contact with the ground at heel strike. Walking with a wearable robotic exoskeleton also increases the energy expenditure need (ie, *aerobic exercise*) [57-59]. By coupling these types of exercises, walking with a wearable robotic exoskeleton may lead to beneficial cardiorespiratory, musculoskeletal, and endocrine-metabolic [60,61] adaptations in WU_SCI_. In addition, a growing body of evidence suggests that cognitive and executive [62] as well as psychological [63,64] benefits can be anticipated, as favorable associations with physical activity, especially aerobic exercise, have been documented. Also of interest, WU_SCI_ have expressed high levels of satisfaction with wearable robotic exoskeleton–assisted walking programs and have positively perceived the wearable robotic exoskeleton learnability and usability [64]. To what extent these health benefits may have positive synergistic effects on their functional capacities and psychosocial well-being is unclear. How to best configure wearable robotic exoskeleton–assisted walking programs (eg, number, frequency, duration, and intensity of sessions) while conciliating them with the perspectives of WU_SCI_ to potentiate the outcomes of such programs also remains elusive.

**Figure 1 figure1:**
[figure not shown]
Wearable robotic exoskeleton for sit-stand transitions and overground walking manufactured by Ekso Bionics.

### Objectives

The *overall goals* of this study, using mixed methods, are as follows: (1) to determine the immediate and short-term effects of a 16-week overground wearable robotic exoskeleton–assisted walking program on organic systems, functional capacities, and multifaceted psychosocial factors among WU_SCI_ living in the community, and (2) to determine self-reported satisfaction and perspectives with regard to the intervention and the device. The *specific objectives* are articulated around four research questions and hypotheses:

Question 1: Does a 16-week walking program with the wearable robotic exoskeleton induce beneficial changes on musculoskeletal, cardiorespiratory, and endocrine-metabolic health; wheelchair-related functional skills and mobility; and psychosocial outcomes? Hypothesis 1: It is hypothesized that beneficial effects observed during the postintervention and retention measurement times will significantly and meaningfully exceed any changes observed during the control and preintervention measurement times (ie, T_0_ [control measurement time] vs T_1_ [preintervention measurement time] vs T_2_ [postintervention measurement time] vs T_3_ [retention measurement time]).Question 2: What personal factors best determine and predict the beneficial effects of the walking program with the wearable robotic exoskeleton? Hypothesis 2: It is hypothesized that the individuals with the highest level of SCI and the longest time since the SCI (ie, possibly the best determinants and predictors) will be those who respond best to the walking program.Question 3: What program attributes best determine and predict the beneficial effects of the walking program with the wearable robotic exoskeleton? Hypothesis 3: It is hypothesized that the total number of steps taken will be the best determinant and predictor of the measured changes.Question 4: What are the participants’ satisfaction levels with the walking program and the wearable robotic exoskeleton itself, and what are the expectations regarding its future use in the context of a home- or community-based adapted physical activity program? Hypothesis 4: It is hypothesized that WU_SCI_ will (1) express high levels of satisfaction with the walking program using the wearable robotic exoskeleton and with the wearable robotic exoskeleton itself and (2) report on how they envision its future in the context of home- or community-based use to shape the development of an adapted physical activity program in the future.

## Methods

### Study Design

A prospective, longitudinal, self-controlled interventional study with multiple discrete measurement times will be used to assess outcomes at baseline (ie, preintervention phase), during the intervention, and thereafter (ie, retention phases) (see Figure 2). While this design may contrast with *classic* study designs frequently recommending a separate comparison group to assess efficacy or effectiveness, the use of a separate comparison group was judged as nonideal in the context of this study, based on the challenges linked to the classification and quantification of the severity of SCIs and their heterogeneous consequences [65]. In addition, interventional trials of new technologies document that potential participants are reluctant to participate, refuse to adhere to the requirements of a control group, or withdraw for the most part from a control group [66,67]. To strike an optimal balance between the need to have a control group with the anticipated strong desire of potential participants to engage in the wearable robotic exoskeleton–assisted walking program, while also considering the amount of, and timeline limits linked to, the study’s funding, the study includes a 4-week observation phase prior to the start of the intervention. Since only individuals with a chronic SCI with *stable* overall health status and life habits will be recruited, outcome measures will be assessed at the start and at the end of the 4-week observation phase. These outcome measures will provide data about each participant’s natural variability and will enable us to detect whether the intervention has an effect greater than the underlying natural variability (ie, patient-specific minimal detectable change criteria computed); they will also enable us to test the effects of the intervention (ie, pre- vs postintervention responses). This boosts the ethical acceptability of the project, minimizes the impacts of potential and unmeasured confounding variables, facilitates recruitment, and mitigates the risk of experimental attrition. Lastly, semistructured interviews and an online questionnaire will capture participants’ satisfaction levels and perspectives about the wearable robotic exoskeleton–assisted walking program and the mobility technology in itself (ie, the wearable robotic exoskeleton).

**Figure 2 figure2:**
[figure not shown]
Summary of the design of the study along with the different assessment times. T_0_: control measurement time; T_1_: preintervention measurement time; T_2_: postintervention measurement time; T_3_: retention measurement time.

### Participants and Inclusion and Exclusion Criteria

We aim to recruit a nonprobabilistic consecutive sample of 20 long-term WU_SCI_. The inclusion and exclusion criteria are listed in Textbox 1. Initial screening is conducted by phone to establish eligibility based on criteria developed during the feasibility study. Once deemed eligible from the initial clinical screening, potential participants attend a short assessment to confirm eligibility.

Inclusion and exclusion criteria.Participant-specific inclusion criteria:Adults (≥18 years old)Chronic complete or incomplete traumatic or nontraumatic spinal cord injury (SCI) at least 18 months before enrollmentLong-term manual wheelchair use as primary means for in-house and community mobility (ie, nonambulatory)Understand and communicate in English or FrenchReside or will arrange for temporary housing in the community within 75 km from the main research siteParticipant-specific exclusion criteria:Other neurological impairments aside from those linked to the SCI (eg, multiple sclerosis)Concomitant or secondary musculoskeletal impairments (eg, hip heterotopic ossification)History of lower extremity fracture within the past yearUnstable cardiovascular or autonomic systemRenal insufficiencyPregnancyAny other conditions that may preclude lower extremity weight-bearing, walking, or exercise tolerance in the wearable robotic exoskeletonExoskeleton-specific inclusion criteria:Body mass: ≤100 kgHeight: 1.52-1.93 mPelvis width: 30-46 cmThigh length: 51.0-61.4 cmLower leg length: 48.0-63.4 cmExoskeleton-specific exclusion criteria:Inability to sit with hips and knees at ≥90° flexionLower extremity passive range of motion limitations (hip flexion contracture ≥5°, knee flexion contracture ≥10°, and ankle dorsiflexion ≤–5° with knee fully extended)Moderate-to-severe lower extremity spasticity (score of >3 on the Modified Ashworth Scale)Length discrepancy (≥1.3 cm or ≥1.9 cm at the thigh or lower leg segment, respectively)Skin integrity issues preventing wear of the wearable robotic exoskeleton

### Intervention: Overground Wearable Robotic Exoskeleton–Assisted Walking Program

An Ekso GT (Ekso Bionics) wearable robotic exoskeleton, which has been approved by Health Canada, is used in this study (see Figure 1). At T_1_, participants engage in a wearable robotic exoskeleton–assisted overground walking program that encompasses 34 training sessions offered over a 16-week period. The number of training sessions per week progressively increases to safely and efficiently adhere to the overload principle (see Figure 3). The duration of the training program mimics that of a recent study that confirms for the first time an improvement in bone turnover among individuals with a chronic SCI following a 16-week walking program [39]. The frequency of the training program that progresses from one to three sessions per week matches the latest recommendation from the Physical Activity Guidelines for Adults with SCI, including the new conditional recommendation to engage in at least 30 minutes of moderate-to-vigorous intensity aerobic exercise three times per week for cardiometabolic health benefits [68]. All training sessions are supervised by a certified physiotherapist as well as a physiotherapy assistant as needed [46,53]. During each 60-minute training session, participants perform sit-stand transfers and walk with the wearable robotic exoskeleton and a walking aid (ie, rolling walker or forearm crutches). Verbal and tactile feedback are provided by the physiotherapist as needed.

**Figure 3 figure3:**
[figure not shown]
Progression of the number of training sessions per week during the 16-week walking program.

Total hip areal bone mineral density (aBMD), determined with dual-energy x-ray absorptiometry (DXA) scans performed at T_1_, is used to assign each participant to one of three training regimes based on lower extremity fracture risks [69]: (1) conservative (T-score ≤ –2.5; first session includes a maximum of 300 steps; number of steps progresses up to 10% every week), (2) moderate (–2.5 < T-score < –1.0; first session includes a maximum of 400 steps; number of steps progresses up to 15% every week), or (3) aggressive (T-score ≥ –1.0; first session includes a maximum of 500 steps; number of steps progresses up to 20% every week). Workload is further individualized depending on each participant’s level of proficiency and tolerance; it is progressively and safely increased by modifying walking parameters (eg, number of steps, speed, and duration) or reducing total resting time or level of assistance provided by the physiotherapist to maintain a moderate-to-vigorous training intensity (ie, rate of perceived exertion ≥3/10 on the Modified Borg Scale [70]). Training parameters are recorded at the end of each session (eg, total standing time, total walking time, total number of steps, assistance provided, and rate of perceived exertion). Given the risks of adverse events inherently linked to the use of a wearable robotic exoskeleton [69,71], skin integrity at interface pressure points, particularly at the tibial tuberosity, and signs of inflammation at the ankle and knee joints before and after each training session, respectively, are assessed and any serious adverse events will be reported.

To be considered as having successfully completed the program, at least 75% of the training sessions (ie, 26/34) need to have been completed. To this effect, to assure an optimal attendance rate similar to the one reached during the feasibility study (ie, attendance rate was 97.7%) [72] and to overcome one of the most commonly reported barriers to intervention studies (ie, transportation), participants have three key options: (1) driving their own car or being transported by car by a family member or a friend with free parking provided within 50 meters from the entrance, (2) using public transit, or (3) scheduling trips with the adapted transport free services.

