**Laboratory assessments**						
	**Bone mineral density and architecture**					
		Dual-energy x-ray absorptiometry (hip and lumbar vertebrae)	✓	✓	✓	✓
		Peripheral quantitative computed tomography (proximal tibia, distal femur, and proximal radius)	✓	✓	✓	✓

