### Statistics

#### Sample Size Estimation

The sample size estimate was based on a comparison using the variability of the absolute change (ie, mean ±SD) in both body composition and bone mineral density (ie, main outcomes) measured pre- and postintervention in our preliminary study [61] and computed with a computerized sample size calculator [100]. Considering the self-controlled design of the study, a total of 18 participants are required to have an 80% chance of detecting a significant increase at the 5% level in the leg lean body mass (kg) at the tibia measured by DXA from 14.0 to 15.8 ±2 mg/cm^3^ [61]. Likewise, a total of 18 participants are required to have an 80% chance of detecting a significant increase at the 5% level in the bone mineral density (mg/cm^3^) at the tibia measured by pQCT from 466 to 532 ±70 mg/cm^3^ [61]. Considering the dropout rate of 7.1% found during the feasibility study [46], an additional 2 participants were added for a total sample size of 20 participants.

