#### Quantitative and Qualitative Analyses

Descriptive statistics (eg, mean, SD, and 95% confidence interval) will be calculated for data summarizing sociodemographic characteristics as well as clinical and laboratory outcomes collected at the different measurement times. The normality of all data distributions and the absence of outliers will be verified via the Shapiro-Wilk test of normality and the absence of studentized residuals greater than ±3 SDs, respectively. Whenever applicable, the level of significance will be set at *P*≤.05 for all statistical tests and the data will be analyzed using SPSS, version 25.0 (IBM Corp).

For Hypothesis 1, one-way analysis of variance for repeated measures (ie, normally distributed continuous data) or Freidman tests (ie, non-normally distributed continuous or categorical data) with planned comparisons based on the hypothesis and Bonferroni correction will be conducted to detect significant time effects, with a special interest for the preintervention (T_0_ vs T_1_), intervention (T_1_ vs T_2_), and retention (T_2_ vs T_3_) phases. In accordance with the principles of a classic intention-to-treat approach, all participants will be included in the final analyses, regardless of withdrawal, compliance, or unintentional missing data. For missing data, imputation of the mean value for the specific group at the specific assessment time will be used. Per-protocol exploratory analyses will also be performed comparing outcomes for those with walking program compliances of greater than 75% to examine maximum treatment efficacy.

For Hypotheses 2 and 3, Pearson or Spearman correlation coefficients will investigate the strength and direction of the relationships between the overall observed changes ([T_1_–T_2_] / T_1_ × 100) for each personal factor (ie, dependent variable) and the program characteristics (ie, independent variable). Independent variables having reached a critical threshold (*P*≤.25) will then be confronted in a stepwise multiple linear regression analysis to identify the three best predictors for each dependent variable and the coefficient of determination (*R^2^*) of the model. To determine the factors for identifying the best responders to the program, analyses similar to the previous ones will be completed, except that the independent variables will be sociodemographic characteristics, anthropometric parameters, characteristics of the SCI, personal factors, and functional disability.

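### Total steps, the Hypothesis 3 predictor, are capped by baseline hip density without guaranteed adjustment for it, so a step association with bone outcomes may be confounded if density relates to response

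*Protocol article*

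**What the plan says.** **Dose assignment (Intervention section, text after Figure 3).** Total hip areal bone density from the T1 DXA scan "is used to assign each participant to one of three training regimes based on lower extremity fracture risks". In the conservative regime (T-score at or below -2.5) the "first session includes a maximum of 300 steps; number of steps progresses up to 10% every week". The corresponding limits are 400 steps and 15% in the moderate regime, and 500 steps and 20% in the aggressive regime (T-score at or above -1.0). These are ceilings. Workload also depends on each participant's "level of proficiency and tolerance; it is progressively and safely increased by modifying walking parameters".

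**Hypothesis (Objectives).** Hypothesis 3 is that "the total number of steps taken will be the best determinant and predictor of the measured changes".

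**Analysis (Quantitative and Qualitative Analyses).** For Hypotheses 2 and 3, correlations relate percentage change from T1 to T2 "for each personal factor (ie, dependent variable) and the program characteristics (ie, independent variable"). Variables with P≤.25 go on to a stepwise regression that identifies the three best predictors. To find the best responders, "analyses similar to the previous ones will be completed, except that the independent variables will be sociodemographic characteristics", together with anthropometric parameters, SCI characteristics, personal factors and functional disability. Hip density, T-score and training regime are not named in either analysis.

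**Outcomes.** The sample size section calls "both body composition and bone mineral density (ie, main outcomes"). Table 1 lists "Dual-energy x-ray absorptiometry (hip and lumbar vertebrae") at all four visits.

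**The concern.** The dose limit is a function of a baseline bone measurement. People with denser hips may start with more steps and progress faster, so total steps will tend to rise with T1 hip density. If density, or something that travels with it, is also related to how bone responds, a crude association between steps and bone change mixes two things: what the steps did, and who was allowed to take them. The mixing can go either way. A positive density-response relation would inflate a step effect or create one. A negative relation would hide a real one.

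The bone outcomes are where this is most plausible. Bone density is a main outcome, and hip DXA both assigns the regime and is itself an outcome. Question 3 asks which program attributes drive benefit, and the Discussion lists the influence of those attributes among the things the study investigates. A reader shown that more steps went with more bone gain could not tell a dose effect from a difference between regimes in the people assigned to them.

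**Working it through.** The article gives no figure for this point, so there is none to reproduce. The check has three steps.

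**1. How far apart do the ceilings push total steps?** From the article: starts of 300, 400 and 500; weekly growth g of 10%, 15% and 20%; 34 sessions in 16 weeks. Assumed, because Figure 3 is not shown: one session a week for 4 weeks, two for 6, three for 6 (4 + 12 + 18 = 34). The limits are read per session.

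The ceiling in week w is start × (1 + g)^(w−1). The permitted total is the sum over weeks of sessions × the smaller of that ceiling and a common plateau P.

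| Plateau P (steps per session) | Conservative | Moderate | Aggressive | Aggressive ÷ conservative |
|---|---|---|---|---|
| 600 | 18,669 | 19,989 | 20,300 | 1.09 |
| 1,000 | 24,897 | 30,856 | 32,684 | 1.31 |
| 1,200 | 26,022 | 35,384 | 38,358 | 1.47 |

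With no plateau the ratio would be 115,500 ÷ 26,181 = 4.41. That implies 500 × 1.20^15 = 7,704 steps in the last 60-minute session, about 128 per minute, so it is not used.

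**2. How strongly could steps track hip density?** Simulation of 20,000 studies of n = 20. Assumed: T-score normal with mean -2.0 and SD 1.2; regimes by the article's cut-offs; a personal plateau uniform on 400–1,000 (A) or 600–1,200 (B) steps per session. Three progression variants:
- (0) everyone at the maximum;
- (1) start at 60%–100% of the maximum, growth at 30%–100% of the limit, attendance 26/34 to 34/34;
- (2) start at 40%–100%, growth at 0%–100%, same attendance.

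The correlation r of T-score with total steps, for variants 0/1/2, is 0.23/0.51/0.46 in A and 0.45/0.63/0.50 in B.

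**3. What does that do to the step test?** Let b be the density-response correlation, with no true step effect. The expected spurious correlation of steps with response is about b × r. For b = 0.5 and r = 0.63 it is 0.5 × 0.63 ≈ 0.31, and the simulation gives 0.31. Proportion of studies with P≤.05 for steps as the only predictor (variants 0/1/2):

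| b | A, unadjusted | B, unadjusted | Adjusted for T-score |
|---|---|---|---|
| 0 | about 5% | about 5% | about 5% |
| ±0.3 | 6/10/9% | 9/13/10% | about 5% |
| ±0.5 | 7/19/16% | 16/28/18% | about 5% |

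A re-run of these scenarios gave the same step totals, the same correlations and the same ranges.

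**Sensitivity to the step model.** A different assumption uses no plateau, a quarter of the permitted growth (last-week ceilings 434, 695 and 1,039) and achieved steps at 50%–100% of the ceiling. It gave 15% at ±0.3 and 34%–35% at ±0.5, again about 5% after adjustment. With a true standardised step effect of 0.40, the mean crude correlation ran from 0.07 (b = -0.5) to 0.67 (b = +0.5). The ranges in the table are therefore examples and not bounds.

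**The case against.** The strongest reply is that the link that creates confounding is not documented. The article says nothing about whether hip density affects response. The bone outcome used for the sample size is tibial pQCT, so a relation between hip and tibia has to be assumed as well. If density is unrelated to response, the crude test keeps its 5% error rate and adjustment only loses precision. This stands, and it makes the point conditional.

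A second reply is that a condensed article leaves covariates to the full plan, and that the set of program characteristics is open and could include the training regime. This stands in part. A reader might infer that the plan rules out adjustment, but the text does not say so. What the text does describe is program characteristics in one analysis and personal factors in another, with entry decided by a P≤.25 screen and stepwise selection. Regime could be a candidate beside steps, but nothing keeps it in the model.

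Third, the simulated rates are not those of the planned procedure. They concern steps as the sole predictor at P≤.05. The plan screens several attributes and ranks them, and some of those, such as walking time, may also vary with regime. Whether the ranking is distorted was not computed. This stands too.

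**Conclusion.** The point holds in conditional form, as something to consider. The ceilings tie total steps to T1 hip density, and the stated analyses do not guarantee adjustment for density or regime. For bone outcomes the step association may therefore be confounded in either direction if density is related to response.

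The illustrated size, for plateaus of at most 1,200 steps, is a false-positive rate of 6% to 13% at a correlation of 0.3 and 7% to 28% at 0.5, against about 5% with no density effect or after adjustment. It rests on an assumed session schedule, T-score distribution, plateaus, progression and density effect.

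A reader might go further and infer that the step result will be biased, or that its direction can be predicted. The article supports neither: it gives no density-response relation and no achieved step counts, and individualised workload may weaken the link between steps and density. Nor does the point extend with the same force to the non-bone outcomes.

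**What to change.** For the bone outcomes only, add an exploratory Hypothesis 3 model of change on total steps with T1 total hip areal density as a continuous covariate. Force the covariate in, exempt from the P≤.25 screen and the stepwise selection, and report the model beside the planned result. A T-score would serve equally if computed on one scale for everyone; the Bone Mineral Density and Architecture section says the software gives z scores or T-scores according to age, so raw density is simpler.

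State in advance how the pair will be read: a step effect on bone is described as dose-related only if it persists after adjustment. Even then it is not causal, because the remaining step variation partly reflects proficiency and tolerance.

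No new data are needed, since hip density and session step counts are already recorded. The cost is one degree of freedom and a less precise step estimate at n = 20. The standard error grows by roughly 1/√(1 − r²): 1.03 at r = 0.23 and 1.29 at r = 0.63. It reaches about 1.5 at r = 0.74, which arose only when plateaus of up to 3,000 steps were allowed. Where density is in fact irrelevant this is a pure loss of power, which is why the adjusted model should sit beside the planned one and not replace it.
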